### Screening and recruitment

Patients in the participating units will be screened daily. Demographic data on screened patients, regardless of meeting enrollment criteria, will be recorded (registry: age, gender and type of surgery). If the patient is determined to be eligible according to the study criteria, he/she will be submitted to a CT scan of the abdomen without contrast media. If the parameters of the defect are suitable, then the patient will be enrolled.

### Patient consent

According to local regulations, all patients or legal representatives have to provide written informed consent before inclusion in the study. Patients will be asked to sign the consent form specific to the type of surgery performed as well as the form for randomization. Every patient will receive a letter to inform his/her general practitioner of enrollment in the study.

### Blinding

Every patient will be informed that he/she will undergo a mesh repair of the abdominal wall defect and will be informed of the type of approach used (laparoscopic or open), but he/she will not be informed of the type of repair adopted (reconstruction or bridging) nor of the type of hypothetical advantages of the technique. The patient will be informed of the complications, recurrence rate and sequelae of a typical incisional hernia repair with mesh.

Postoperatively, the examiner executing the physical and QOL-related tests will be blinded to the type of surgery received by the subjects. He/she will be a resident or physician who was not involved in the operation and will examine the patient with dressings on. During the hospital stay, the patient will have a wide dressing on the surgical wound.

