### Setting

Patients will be enrolled at six different surgical units across Italy, tertiary referral centers for both laparoscopy and abdominal wall surgery (three university teaching hospitals). The involved surgeons are experienced in the field of abdominal wall reconstruction and advanced laparoscopic techniques and have treated at least 20 cases for each trial procedure [21].

At least two investigators from each participating center will be involved in the study. One researcher will receive the allocation treatment for the patient after calling the statistician of the main investigation center (University of Genoa). The other investigator, blinded to the randomization arm, will score the primary and secondary postoperative endpoints.

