### Performance and measures: double leg-lowering test (DLL: how and when)

A. In a supine position, the patient raises both legs; the movable arm of a goniometer is held tightly against the longitudinal axis of the patient’s lateral thigh by the examiner’s hand. As the patient lowers the legs, the examiner notes the angle between the extended legs and the table at the moment the pelvis tilts anteriorly and the lower back arches off the table. This angle is subtracted from 90° to determine the angle of interest.

The instrument used for the DLL test is the Jamar E-Z Read Goniometer 12/32 cm (Figure 1), which has a scale from 0° to 180° and from 0° to 360° in 1° increments (inch and centimeter linear measurements). The instrument is made with transparent plastic, making it easy to observe the joint as it moves through the range of motion.

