**Figure 1 F1:**
[figure not shown]
Jamar E-Z Read Goniometer 12/32 cm.

To obtain a more precise and less variable measurement, before performing the test, three colored dots will be applied to the hip and ankle of the patients and on the underlying surface. During the test, a picture of the patient will be shot at maximum leg rise. Using the dots as reference points, the angle will be measured with computer software directly on the picture.

After measuring the angle, a score will be assigned for the calculation of AWS (5 points).

B. The test will be performed preoperatively and at 1 month, 6 months and 12 months postoperatively.

•41° or more (normal) 5 points

•31°-40° (good) 4 points

•21°- 30° (fair) 3 points

•11°-20° (poor) 2 points

•0°-10° (trace) 1 point

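### The only dressing period stated is the hospital stay, yet every postoperative DLL and TR test, including the 12-month primary outcome, comes later, so examiner masking at those tests is not secured

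*Protocol article*

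**What the plan says.** The protocol article sets out the masking of outcome assessment in two places.

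- Blinding: "the examiner executing the physical and QOL-related tests will be blinded to the type of surgery received by the subjects". On who this is and how masking is kept: "He/she will be a resident or physician who was not involved in the operation and will examine the patient with dressings on". The section then adds: "During the hospital stay, the patient will have a wide dressing on the surgical wound".
- Setting: one investigator per centre receives the allocation, and a second one does the scoring: "The other investigator, blinded to the randomization arm, will score the primary and secondary postoperative endpoints".

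The Blinding section also says that the patient "will be informed of the type of approach used (laparoscopic or open"), although not whether the repair was a reconstruction or a bridging.

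The DLL section gives the timing: "The test will be performed preoperatively and at 1 month, 6 months and 12 months postoperatively". The TR section gives the same times. The Primary outcome section names the change in DLL at 12 months, and the Follow-up section places that visit at day 360 ± 3.

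On the reading itself, "the examiner notes the angle between the extended legs and the table at the moment the pelvis tilts anteriorly" and the lower back lifts. The text under Figure 1 adds coloured reference dots and a photograph on which software measures the angle.

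**The concern.** The article describes a physical means of hiding the wound, and the one period it attaches to that means contains no postoperative DLL or TR test. If the abdomen is uncovered at 1, 6 and 12 months, the examiner may be able to tell the arm from new scars or from what the patient says.

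Approach and arm are the same thing in this trial: under Interventions, open surgery is the reconstruction group and laparoscopic surgery the bridging group. Because patients know their approach, much of what the single-blind label promises for the primary outcome depends on the examiner. The DLL also depends on patient effort and on how the test is run, so knowledge of the arm could shift the readings. In a non-inferiority comparison with a 5-degree margin, a shift of a degree or two is not negligible.

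**Working it through.** **Step 1. Masking period against test schedule.**

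| Item | Period or time | Section |
|---|---|---|
| Wide dressing | Hospital stay | Blinding |
| Examination with dressings on | No period stated | Blinding |
| Post-surgical belt (against seroma, not for masking) | 30 days | Postoperative |
| DLL after surgery | 1, 6 and 12 months | DLL section |
| TR after surgery | 1, 6 and 12 months | TR section |
| Primary outcome | 12 months | Primary outcome |

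The stated dressing period covers 0 of the 3 postoperative test times. The belt has ended well before 6 and 12 months. No section says how the abdomen is covered at the outpatient tests, and none asks patients to keep their approach from the examiner.

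**Step 2. What could reveal the arm.** The Surgical period section describes trocar sites in the bridging group and an open wound in the reconstruction group. Eligible patients have a midline incisional or a primary ventral hernia. Those with a midline incisional hernia would be expected to have a midline scar already in either arm, so new trocar scars are the likely clue. In primary ventral hernia a new midline scar could be one as well. The second route is the patient's own knowledge of the approach.

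**Step 3. The plan's own sample size.** Inputs from the sample size section: margin 5 degrees, SD 8.5 degrees, power 90%, alpha 5% (sidedness not stated), 50 per arm.

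- One-sided 5%: n = 2 × [8.5 × (1.645 + 1.282) / 5]² ≈ 49.5, so 50 per arm. This reproduces the plan.
- One-sided 2.5%: the same formula with 1.960 gives 61 per arm.

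The one-sided 5% reading is therefore used below.

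**Step 4. What a reading bias would do.** The documents give no size for any bias; 1 and 2 degrees are assumptions.

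- SE of the difference = 8.5 × √(2/50) = 1.70 degrees.
- False non-inferiority when bridging is truly worse by the margin, with bias b in its favour: Φ(b/1.70 − 1.645).
- Power when the arms are truly equal, with bias b against bridging: Φ((5 − b)/1.70 − 1.645).

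| Assumed bias b | False non-inferiority (bias for bridging) | Power (bias against bridging) |
|---|---|---|
| 0 degrees | 5.0% | 90.3% |
| 1 degree | 14.5% | 76.1% |
| 2 degrees | 32.0% | 54.8% |

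If the test were run at one-sided 2.5%, a bias of 1 degree for bridging would raise the error from 2.5% to 8.5%, and 2 degrees to 21.7%.

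**The case against.** A reader might infer that the dressing is the only masking device and that the examiner is plainly unmasked at 12 months. The documents do not support that, for these reasons.

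- The statement that the examiner "will examine the patient with dressings on" has no time limit, and its subject is the person doing the physical tests. It can be read as covering all three outpatient tests, with the hospital dressing as an additional measure. This stands as an ambiguity. It does not settle the matter, because a healed wound is not ordinarily dressed a year after surgery and the only period given is the hospital stay.
- Masking also rests on an examiner who took no part in the operation and on a scorer separate from the investigator who receives the allocation. This stands. Neither measure hides a scar or stops a patient from naming the approach.
- The angle is measured by software on a photograph, which makes the reading more objective. This stands in part. The examiner still runs the test, no masked off-site reader is named, and the photograph is described at the greatest leg elevation, whereas the angle of interest is defined at the moment of pelvic tilt.

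A reader might also infer that a midline scar gives the arm away in general. For incisional hernias it does not, since an earlier scar is expected there in both arms.

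Nor do the documents show that bias would favour non-inferiority. The trial's hypothesis is that bridging is similar, but the Background reports that expert groups recommend midline re-approximation and that several surgeons see such techniques as the standard. An examiner could lean either way.

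Finally, a journal article may leave the type of cover and similar details to the full protocol. That is fair for the details. The point here is that the article does state a means of concealment with a period, and that period does not reach the primary endpoint.

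**Conclusion.** The point holds as a weakness in how masking is fixed, not as proof that masking fails. The stated dressing period includes none of the postoperative DLL and TR tests, and patients hold information that identifies the arm. The separate scorer, the uninvolved examiner and the photograph lower the risk but leave a realistic route to unmasking at the 12-month primary test.

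The sizes in the working are illustrations. They rest on the plan's SD and 50 per arm, a normal approximation, a one-sided 5% test, and an assumed uniform shift between arms. On those terms each degree of bias matters: in one direction it multiplies the error rate nearly threefold (5% to 14.5%), and in the other it removes about 14 percentage points of power (90.3% to 76.1%). The sample size is not affected. The change is worth making because it is cheap and protects the primary outcome.

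**What to change.** State in the Blinding section that at the 1-, 6- and 12-month DLL and TR tests:

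1. every patient in both arms wears the same opaque abdominal cover, put on before the examiner enters and kept on for the photograph;
2. patients are told beforehand not to disclose their surgical approach to the examiner.

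Optionally, the examiner records a guess of the arm after the 12-month test, so that the success of masking can be reported.

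The cost is a change of wording, an inexpensive cover and a few minutes per visit. No extra staff, procedure or patients are needed.

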### Interventions: surgery

The patient will be divided into two groups according to the randomized procedure:

Group R (reconstruction)

The planned number of patients will be submitted to a Rives-Stoppa procedure for the repair of the defect [22].

Group B (bridging)

In this group, after randomization patients will be operated on using a standard laparoscopic technique [23].

### Mesh

To minimize the effect due to different materials and density, every center will be encouraged to use the same type of mesh. A composite, lightweight, polypropylene mesh suitable for both retromuscular and intraperitoneal repair should be adopted.

### Fixation methods

The mesh will be sutured in Group R with standard, non-resorbable passing sutures. In Group B, absorbable tacks placed with the double crown technique and reinforced with fascial sutures will be used.

### Perioperative management

#### Before surgery

Patients will be admitted the day before or on the day of surgery. Patients under antiplatelet and warfarin therapy will be instructed to stop therapy 7 days before surgery. Low-molecular-weight heparin will be administered according to thrombosis risk. No bowel preparation will be required. According to national guidelines, the patients will be submitted to a single dose of a first- or second-generation cephalosporin (e.g., cefazolin 2 g) as antibiotic prophylaxis at the moment of induction of anesthesia. This dose will be repeated according to the duration of surgery [24]. In cases of different bacterial or high-risk settings, the final decision on antibiotics will be left to each individual surgeon.

### Surgical period

Group B will not use any surgical drain (laparoscopic group). Group R will be allowed to use drains according to the surgeon’s discretion [25]. Patients in group B will receive a local anesthetic for each trocar insertion site (ropivacaine HCl, 0.75%, 5 ml each). In group R, the patients will receive anesthetic in the whole wound (ropivacaine HCl, 0.75%, 15 ml). A bladder catheter will be inserted in the ward to assess intraabdominal pressure with a transducer. The catheter will be removed on the first postoperative day after the final measurement of intraabdominal pressure.

### Postoperative

Postoperative pain control is planned with the elastomeric pump infusion of painkillers. Parenteral opioids will be used for rescue analgesia. Patients will be allowed liquids on the night of surgery, a semisolid diet on the first postoperative day and a light meal on the second. In case of unplanned resection, the decision will be left to operating surgeon. Patients will be discharged when they are conscious and orientated, able to tolerate a solid diet, have regular bowel functions and are able to take care of themselves.

Postoperative medications:

Low-molecular-weight heparin will be prescribed for deep venous thrombosis and pulmonary embolism prophylaxis. Painkillers and antibiotics will be prescribed based on the patient’s needs. Patients will also be prescribed a post-surgical belt for 30 days to minimize seroma formation.

### Follow-up

The patient will be submitted to a 1-year postoperative follow-up. Planned follow-up visits will be on the following days:

•10 ± 3 days (wound evaluation and clinical evaluation)

•30 ± 3 days (clinical evaluation and study test performance)

•180 ± 3 days (clinical evaluation and study test performance)

•360 ± 3 days (clinical evaluation and study test performance)

### Outcomes

#### Primary outcome

Changes in baseline DLL measures at 12 months postoperatively in both groups.

#### Secondary outcome

Among the subjects in each group of treatment, the secondary outcomes are as follows:

•differences in DLL (preoperation and at 1 and 6 months postoperation)

•differences in TR test (preoperation and at 1, 6 and 12 months postoperation)

•AWS score (preoperation and at 1, 6 and 12 months postoperation)

•respiratory function tests (preoperation and at 6 and 12 months postoperation)

•intraabdominal pressure (preoperation and postoperation)

•pain

•quality of life (SF36, preoperation, postoperation, 1 month postoperation, 6 months postoperation and 12 months postoperation)

•recurrence rate in each group

### Performance and measures: double leg-lowering test (DLL: how and when)

A. In a supine position, the patient raises both legs; the movable arm of a goniometer is held tightly against the longitudinal axis of the patient’s lateral thigh by the examiner’s hand. As the patient lowers the legs, the examiner notes the angle between the extended legs and the table at the moment the pelvis tilts anteriorly and the lower back arches off the table. This angle is subtracted from 90° to determine the angle of interest.

The instrument used for the DLL test is the Jamar E-Z Read Goniometer 12/32 cm (Figure 1), which has a scale from 0° to 180° and from 0° to 360° in 1° increments (inch and centimeter linear measurements). The instrument is made with transparent plastic, making it easy to observe the joint as it moves through the range of motion.

**Figure 1 F1:**
[figure not shown]
Jamar E-Z Read Goniometer 12/32 cm.

To obtain a more precise and less variable measurement, before performing the test, three colored dots will be applied to the hip and ankle of the patients and on the underlying surface. During the test, a picture of the patient will be shot at maximum leg rise. Using the dots as reference points, the angle will be measured with computer software directly on the picture.

After measuring the angle, a score will be assigned for the calculation of AWS (5 points).

B. The test will be performed preoperatively and at 1 month, 6 months and 12 months postoperatively.

•41° or more (normal) 5 points

•31°-40° (good) 4 points

•21°- 30° (fair) 3 points

•11°-20° (poor) 2 points

•0°-10° (trace) 1 point

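### The double leg-lowering (DLL) angle, the primary endpoint, is defined at pelvic tilt during lowering, but the photograph used to measure it is taken at maximum leg rise; the two instructions contradict each other

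*Protocol article*

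**What the plan says.** The Primary outcome section names "Changes in baseline DLL measures at 12 months postoperatively in both groups". The section on performance of the double leg-lowering test then gives two accounts of how the angle is obtained.

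- **Definition.** The patient raises both legs and lowers them, and "the examiner notes the angle between the extended legs and the table at the moment the pelvis tilts anteriorly and the lower back arches". The reading is then converted: "This angle is subtracted from 90° to determine the angle of interest". A goniometer is named as the instrument.
- **Photographic step, below Figure 1.** This is introduced as an improvement: "To obtain a more precise and less variable measurement, before performing the test, three colored dots will be applied" to hip, ankle and underlying surface. The timing follows: "During the test, a picture of the patient will be shot at maximum leg rise". The reading is then taken from it: "Using the dots as reference points, the angle will be measured with computer software directly on the picture".

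The rule for assigning 1 to 5 points comes directly after the photographic step. Those points supply up to half of the 10-point abdominal wall strength (AWS) score. The article mentions no second picture at pelvic tilt and does not say whether the goniometer or the software value enters the analysis.

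**The concern.** In a test where the legs are raised and then lowered, maximum rise comes before any lowering. An angle taken there shows how high the legs went. It does not show how far they came down before the pelvis tilted, which is what the test is meant to capture.

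The photograph is presented as the more precise method, so a careful site has reason to prefer it. If it does, the value on its case report form is not the DLL that the protocol defines. With six surgical units and two incompatible instructions, different units could also record different quantities under one name.

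This matters more because the trial is designed as non-inferiority. The Clinical implications section would read similar test results in the two arms as showing that anatomic repair offers no advantage. An endpoint that responds poorly to abdominal wall function could contribute to such similarity.

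**Working it through.** **1. The plan's own figure.** The sample size section gives a margin of 5°, an SD of 8.5°, 90% power, alpha 5% and 50 patients per arm. With a true difference of zero and one-sided alpha 0.05:

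n = 2 × (1.645 + 1.282)² × 8.5² / 5² ≈ 2 × 8.56 × 2.89 ≈ 49.5, rounded up to 50 per arm.

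The figure reproduces. The arithmetic does not depend on when the picture is taken, but the margin and SD were set for DLL. No SD is given for an angle at maximum rise, so no sample size can be worked out for that quantity.

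**2. The two instructions in symbols.** Let S be the leg-table angle at maximum rise and T the angle at pelvic tilt.

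- Defined DLL = 90 − T.
- Photographic value = 90 − S, or S itself if the subtraction is not applied to the picture.
- Defined DLL minus photographic value = (90 − T) − (90 − S) = S − T.

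S − T is the arc lowered before the pelvis tilts. It is within 5° only for a patient who tilts within 5° of starting to lower.

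**3. Change from baseline.**

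- Defined change at 12 months = T(baseline) − T(12 months).
- Photographic change, with the subtraction = S(baseline) − S(12 months).

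T does not appear in the second line. Invented example: S is 85° at both visits and T moves from 60° to 50°. Defined DLL goes from 30° to 40°, a change of +10° (3 points to 4). The photographic value is 5° both times, a change of 0° (1 point both times).

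**4. Score bands.** The documents give no value for S, so a range is shown.

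| Assumed rise S | 90 − S | Points | Points if not subtracted |
|---|---|---|---|
| 80–90° | 0–10° | 1 | 5 |
| 70–79° | 11–20° | 2 | 5 |
| 60–69° | 21–30° | 3 | 5 |

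Under the 90-minus rule, the top band (41° or more) needs a rise of no more than 90 − 41 = 49°, so a poorer raise earns a better score. Without the subtraction, any rise of 41° or more scores 5. By contrast, tilt at 60° gives 30° (3 points) and tilt at 40° gives 50° (5 points), so the angle at tilt does separate patients across the bands.

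**The case against.** The strongest reply is that the photograph's timing is simply misworded. The definition is explicit, the goniometer is named as the instrument, and the angle measured on the picture can be read as the angle just defined. The bands suit 90° minus the tilt angle. If patients do raise their legs to near vertical, a literal reading with the subtraction would score nearly everyone in the lowest band, which examiners should notice early. This is plausible, and it limits the finding to a contradiction in the text. It does not remove it, because nothing in the article supports reading maximum rise as pelvic tilt.

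A reader might also infer more than the documents support:

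- **That the endpoint has in fact been mis-measured.** The text shows conflicting instructions, not what sites did.
- **That the error is 30° or more, several times the margin.** This needs an assumed start angle near vertical and a patient of normal strength; for a patient who tilts almost at once, the two values nearly coincide. It also sets one person's offset against a between-arm margin on change from baseline, where a fixed offset would cancel. What survives is the loss of sensitivity: S − T is not fixed but moves with T.
- **That the photographed angle is unrelated to the repair and so must favour bridging.** No passage shows that raising the legs is independent of the abdominal wall. Randomization is stratified by center, so a unit using one method throughout applies it to both arms. That points to dilution or noise rather than a built-in advantage for one arm.

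**Conclusion.** The contradiction is certain and concerns the measurement of the primary endpoint and the DLL part of the AWS score. It is an inconsistency in what the article states, not a detail that an article would leave to another document.

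Its effect on results is conditional. If the photographic instruction is followed literally, the recorded value is not the defined DLL and is insensitive to it, the margin and SD cannot be carried over, and lost sensitivity may tend towards a finding of no difference. If sites read the angle at tilt in spite of the wording, the harm is small. The documents do not show which applies. The point scores above rest on assumed start angles and are illustrations, not estimates of error.

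The correction should be made before further measurements. The dots mark only hip, ankle and surface, so a still taken at maximum rise cannot later be re-read for the angle at tilt.

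**What to change.** 1. Amend the text below Figure 1 so that the picture, or a frame from a short video, is taken at the moment of anterior pelvic tilt and lumbar arching during lowering.
2. State that the 90-minus rule applies to the angle measured on that image.
3. Name one reading, image or goniometer, as the analysed primary value for all centres and visits. Either choice resolves the contradiction; what matters is that it is fixed and uniform.
4. For patients already photographed at maximum rise, use the recorded goniometer reading at tilt where there is one, and flag the rest.

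For future measurements the cost is low: a short amendment, a matching case report form entry and a note to the six units. A timed still needs no new equipment, and video is optional.

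For patients already measured the cost may be higher. Enrolment began in June 2013, and a preoperative baseline cannot be repeated after surgery. Any operated patient without a goniometer reading at tilt has no valid baseline for the primary outcome. The article does not say how many there might be, so the sponsor should count them now.
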